**Infant**				
**Development**	Ages & Stages Questionnaires, Third Edition (ASQ-3)	The ASQ-3 is a parental-reported developmental screening tool that shows high reliability, internal consistency, sensitivity, and specificity. It is available in English and Spanish. **Measurement units:** Continuous: 5 subscale scores (5 areas; communication, gross motor, fine motor, problem solving, personal-social) Categories: typical development or need for monitoring/further assessment **Analysis:** Compare the mean/median and SD/IQR scores of sub scales and categories	- Postpartum (12 months)	[51, 52]
**Physical activity**	Two question items—sedentary/screen time and outdoor play	Infant physical activity at 12 months of age will be assessed using two question items: one on sedentary time including screen time over a typical week and time spent in situations that restrict movement (e.g. stroller, playpen) and one on the amount of activity about the number of hours the child typically spends playing outdoors on weekdays and weekend days. **Measurement units:** Continuous: time spent sedentary or playing (minutes) Categories: meeting guidelines **Analysis:** Compare the mean/median and SD/IQR and meeting guidelines (yes/no)	- Postpartum (12 months)	
**Diet**	Complementary Food Frequency Questionnaire (CFFQ)	The CFFQ comprises 49 food items under six food categories which measures what the infant consumed over the last 4 days. Breastmilk and formula intakes are also measured in this validated tool. **Measurement units:** Continuous: nutrient values Categories: meeting dietary guidelines **Analysis:** Compare the mean/median and SD/IQR and meeting guidelines (yes/no)	- Postpartum (12 months)	[53]
**Health status**	Patient-Oriented SCORing Atopic Dermatitis (PO-SCORAD)	Incidence of infections, eczema, and atopic dermatitis will be assessed using the PO-SCORAD, a self-assessment tool for use by parents which has been validated in 12 European countries. **Measurement units:** Continuous: PO-SCORAD Score (0–90) Categories: incidence of infections, eczema, and atopic dermatitis (yes/no) **Analysis:** Compare the mean/median and SD/IQR and incidences	- Postpartum (12 months)	[54]
**Health costs**	Adapted questionnaires from the InFANT Extend Study and the Infant Feeding Practices Study II	Participant employment, childcare, and out of pocket costs will be estimated by self-completed questionnaires derived from the Infant Feeding Practices Study II. Health costs for the child will be assessed using an adaption of the instrument used to assess costs in the InFANT Extend Study. The questionnaire covers health costs, travel costs, and lost productivity during the antenatal and postpartum periods. **Measurement units:** Continuous: productivity loss (absenteeism and presenteeism), out-of-pocket costs Categorical: employment status, childcare status, high/average/low costs, and productivity losses **Analysis:** Compare the mean/median and SD/IQR and groups	- Postpartum (3, 6, 9, 12^a^ months)	[37, 55]
**Sleep**	Brief Infant Sleep Questionnaire (BISQ)	Sleep duration, night wakings, and method of falling asleep will be measured using the BISQ which is available in English and Spanish. **Measurement units:** Continuous: time spent asleep/awake (minutes) and sleep behaviour scores Categorical: problem sleeper (yes/no), meeting sleep recommendations (yes/no) **Analysis:** Compare the mean/median and SD/IQR and groups	- Postpartum (3, 6, 9, 12^a^ months)	[56]

For measurements collected at more than one time point

^a^The primary outcome of interest

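### Table 1 takes the yes/no incidence of infant infections and eczema from a single 12-month atopic dermatitis score, with no infection item and no look-back period named

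*Protocol article*

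**What the plan says.** In Table 1 of the protocol article, the infant Health status row names one instrument, "Patient-Oriented SCORing Atopic Dermatitis (PO-SCORAD"). Its description reads: "Incidence of infections, eczema, and atopic dermatitis will be assessed using the PO-SCORAD", and adds that parents complete it. Two outputs follow: a continuous score from 0 to 90, and a yes/no classification, "Categories: incidence of infections, eczema, and atopic dermatitis (yes/no"). The analysis entry is "Compare the mean/median and SD/IQR and incidences". The only time point is the 12-month postpartum assessment.

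Other infant rows of the same table are repeated. For sleep, "Sleep duration, night wakings, and method of falling asleep will be measured using the BISQ", and that row is scheduled at 3, 6, 9 and 12 months. Health costs follow the same schedule.

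The secondary outcomes listed under Outcome measurements include infant growth, development, diet, breastfeeding and activity. Infections and eczema are not in that list.

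**The concern.** Two things in the row do not fit together.

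- **Construct.** Infections are assigned to a tool whose name says that it scores one skin condition. No question about infections is mentioned.
- **Time.** Incidence means new cases over a period. The row gives no period, and a severity score taken once describes a state, not a count of new cases.

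If the row is followed literally, the infection comparison has no valid source, and a dermatitis score would be reported between arms under the label of incidence. This could mislead because the coaching content covers breastfeeding and formula feeding (Intervention section) and breastfeeding is itself a secondary outcome. Infant infection and eczema results are therefore likely to be reported beside it. A difference, or the lack of one, would then be credited to a quantity that was not measured.

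**Working it through.** The plan states no rate, recall window or power for this outcome, so there is no figure to reproduce. The check is mainly a comparison of entries.

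**1. Does Table 1 name ad hoc questions where it uses them?** Yes. Infant physical activity is described as two question items, and the maternal breastfeeding row lists a scale and, separately, adapted survey questions. The infant Health status row lists only the PO-SCORAD.

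**2. Does Table 1 give recall windows?** Often. The maternal food questionnaire covers the previous month, the maternal sleep index one month, and the infant food questionnaire four days. The infant Health status row gives none.

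**3. Could another listed source supply infections?** Not as described.
- The health-cost questionnaire (3, 6, 9 and 12 months) is described by costs, travel and lost productivity, not by diagnoses.
- The infant sleep questionnaire covers sleep only.
- Birth assessments cover the time around delivery.
- Parent-reported measurements at 3, 6 and 9 months are weight, length and head circumference.

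So the mismatch is in the stated text and does not depend on an unseen document.

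**4. How much could the recall window matter?** This is an illustration only. It applies to eczema or dermatitis, and only if the yes/no answer reflects the infant's state at 12 months with no look-back. Evaluable infants per arm: 400 × 0.70 = 280 (Sample size section, assuming that infants are retained as mothers are). Assumed: 20% of infants affected at some time before 12 months, the same in both arms. The standard error of the log risk ratio is √(2 × (1/events − 1/280)).

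| Share resolved by 12 months (assumed) | Recorded proportion | Expected events per arm | SE of log risk ratio |
|---|---|---|---|
| 0% | 20% | 56 | 0.169 |
| 40% | 12% | 33.6 | 0.229 |
| 50% | 10% | 28 | 0.254 |
| 60% | 8% | 22.4 | 0.287 |

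Power under the same condition, with 280 per arm and a two-sided 5% test of two proportions (pooled variance under the null, separate variances under the alternative):

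| Share still detectable (assumed) | True 30% vs 20% | True 20% vs 12% |
|---|---|---|
| 100% | 78% | 73% |
| 75% | 62% | 59% |
| 50% | 43% | 41% |
| 25% | 23% | 23% |

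All rates and shares here are assumptions. Nothing comparable can be calculated for infections, because the row names no item that records them.

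**5. Which contacts could still be used?** Recruitment began on 9 February 2021 (Trial status), with enrolment at 12 to 24 weeks' gestation. Assume delivery at 40 weeks.
- A woman enrolled that day at about 24 weeks delivers 16 weeks later, about 1 June 2021. Her 3-, 6- and 12-month contacts fall in early September 2021, early December 2021 and early June 2022.
- A woman enrolled that day at 12 weeks delivers 28 weeks later, about 24 August 2021. Her 3-month contact falls in late November 2021.

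When the article appeared on 28 December 2021, the first enrolees had therefore passed the 3-month contact and some the 6-month contact. No term infant had reached 12 months.

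**The case against.** The strongest reply is that the row is loosely worded, not badly designed. It lists the score and the yes/no categories as separate outputs, and a dermatitis score cannot itself return a yes or no for infections. The yes/no categories may therefore come from parent questions asked alongside the score and set out in a questionnaire or analysis plan that is not shown. A question asking about any episode since birth would capture resolved episodes, subject to recall error. Item wording is also something that an article commonly leaves to fuller documents.

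Part of this stands. A reader might infer that the plan claims first-year incidence and will record every resolved episode as absent. The documents do not support that: no period is stated, and the recall window of the instrument or of any accompanying question is not given. A reader might also take this row for the main infant safety measure. No section presents it as one, infections and eczema are not among the listed secondary outcomes, and infant growth and development are followed separately.

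What does not stand is that the matter is only missing detail. The row does not leave the source open. It says that the PO-SCORAD is how these incidences are assessed. If separate questions exist, that statement is wrong and should be corrected. If they do not, the infection outcome has no source.

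**Conclusion.** The point holds as a mismatch between instrument and outcome. As written, one atopic dermatitis score at 12 months cannot give the incidence of infections, and it cannot be read as incidence of eczema or dermatitis over a period.

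Its size cannot be stated from the documents. The tables above show that precision and power could fall materially if many cases had resolved and nothing asked about them, but they rest wholly on assumed rates and on the absence of a look-back question. They should not be cited as the effect of this plan. The stronger claim, that resolved episodes are missed, remains open until the recall window is stated.

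This is a minor infant outcome, and the primary BMI comparison is unaffected. Correction is worthwhile because it is cheap and because a mislabelled between-arm result is easily over-read.

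**What to change.** 1. In the infant Health status row, report the PO-SCORAD as severity and presence of atopic dermatitis at the 12-month assessment.
2. Take infections and eczema from separately named parent-report yes/no items with a stated look-back, for example since birth, worded the same in both arms, on the 12-month questionnaire. If such items already exist, name them and their recall period in the row.
3. Where contacts are still to come, put matching items on the existing 3-, 6- and 9-month questionnaires, asking about the time since the previous one. Because early enrolees will lack some of these, the since-birth item at 12 months is the natural basis for the between-arm comparison, with the quarterly answers as support.
4. If no such items exist or can be added, remove 'infections' and 'incidence' from this outcome.

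Relabelling costs nothing. New items mean a few extra questions on online forms already in use, and so a slight added burden on participants. The drawbacks are recall error in a since-birth question and incomplete quarterly data for women enrolled early.

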### Baseline assessments

Participants will attend the first study visit after recruitment in line with routine antenatal care. A researcher will facilitate participants in the intervention group with onboarding, including downloading the mHealth coaching app, account creation, and scheduling the initial coaching session. For participants in the control group, the research clinician will provide the women with a written leaflet with details of the approved website and show the woman how to access the health information on the Bump2Baby website. Demographic characteristics will be collected via questionnaire and will include maternal age, ethnicity, gravidity, parity, relationship status, educational attainment, employment status (of the participant and relevant partner), housing status, childcare responsibilities, and prior medical history.

Anthropometric measurements of maternal height (cm) and weight (kg) will be extracted from medical records, and all participants will also be provided with a set of digital scales (Smart Body Fat Scale, RENPHO©) for the duration of the study. Participants will be provided with a manual on how to use the scales appropriately and will be asked to weigh themselves approximately once a week. The scales will connect via Bluetooth, with an app on the participant’s phone, which facilitates automatic recording of this data when the individual is connected to a wireless network. Body mass index (BMI, kg/m^2^) will be calculated from these measurements. Blood pressure will also be measured using a calibrated blood pressure monitor at the baseline visit.

Participants will be asked to complete the online questionnaires, detailed in Table 1, within 1 week of the baseline visit before the first health coaching session for the intervention group.

### Antenatal assessments

Weight will continue to be recorded weekly by participants using the digital scales provided, and gestational weight at 36 weeks (or closest time point) will also be obtained from medical records. If the participant has had an Oral Glucose Tolerance Test (OGTT) at 24–26 weeks’ gestation within their usual care, this result will be taken from the medical records. Foetal ultrasound scan results will also be obtained from medical records, where available. The measurements recorded, where available, will include crown rump length (mm), gestational age (weeks/days at scan), estimated due date, biparietal diameter (mm), abdominal circumference (mm), femur length (mm), estimated foetal weight (g), liquor volume, amniotic fluid index (max pool depth, cm), abdominal fat mass (mm), subscapular fat mass (mm), mid-thigh lean mass (cm^2^), mid-thigh fat mass, umbilical artery pulsatility index, umbilical artery resistive index, and end-diastolic flow.

### Birth assessments

After birth, the following details will be obtained where available from the medical records: gestation (weeks), maternal weight (closest collected to delivery from medical records, kg), delivery method, (including any medical assisted interventions), birth complications (including admission to the special care nursery and/or neonatal hypoglycaemia), placenta weight (g), Apgar score, and anthropometry (birth weight (g), length (cm), and head circumference (cm)).

### Postpartum assessments

It will be encouraged that weight will continue to be recorded weekly by participants using the digital scales provided. Breastfeeding will be assessed using an adapted version of the Australian National Infant Feeding Survey 2010 and InFANT Extend Study questionnaires to assess the history of breastfeeding, and for those that breastfed, their experience of feeding, pumping, and timing over the 3 monthly intervals (3, 6, 9, 12 months) [36, 37]. Psychological health will be assessed by the Edinburgh Postnatal Depression Scale (EPDS) and sleep quality by the Pittsburgh Sleep Quality Index (PSQI) at the same intervals [38, 43]. Parental-report infant weight (kg), length (cm), and head circumference (cm) will be collected at 3, 6, and 9 months. All metrics and questionnaires being completed postpartum are detailed in Table 1.

### 12-month postpartum assessment

At 12 months postpartum, participants will be contacted by the research team to arrange the last study visit. Participants will attend with their infant, and the following measurements will be collected: infant length (cm, assessed using a calibrated length mat), weight (kg), and head circumference (cm). Maternal height will be measured in centimetres and weight in kilograms. Standard operating procedures will be provided for these measurements. BMI *z*-score will be calculated using WHO growth standards [57].

Participants will be asked to complete further questionnaires, as detailed in Table 1, online the week before this appointment.

### Biological samples

Non-fasting blood samples will be taken by phlebotomists or research nurses at the baseline visit (first antenatal appointment) and at the 12-month postpartum visit. Where routine OGTTs are performed antenatally (24–26 weeks) or postpartum (6–12 weeks), an additional blood sample will be taken at the fasting time point for analysis. These will be processed and stored at − 80 °C at the local site until secure transport of all samples to the University College Dublin for assay using standard procedures and laboratory equipment. All assaying will be performed at study completion and will include the following metabolic markers: HbA1c, glucose, and blood lipids (total cholesterol, HDL cholesterol, LDL cholesterol, triglycerides).

### Additional intervention assessments

The following assessments will be carried out in the intervention arm of the RCT:
Fidelity assessment delivery: An mHealth coaching manual has been prepared to detail the a priori behaviour change techniques to be used by the coaches in the synchronous and asynchronous coaching interactions at different determined time points. All coaching interactions, synchronous and asynchronous, will be recorded, in either video or text format as per the type of interaction. A sample of these interactions will be coded and compared to the coaching manual, on an ongoing basis, to provide a continuing feedback fidelity process to the mHealth coaches. For a random sample of participants, all coaching interactions will be coded against the specified coaching manual to generate a fidelity index, so that treatment fidelity can be examined in relation to participant outcomes.Exposure to intervention: All automated and non-automated motivational push notification messages and reminders from the mHealth coaching app and coach will be recorded. The mHealth coaching app platform records which messages within the app are accessed by participants, and this data will be used to determine the total number of messages received by everyone, by message content (information, motivational, reminder). This will be used to generate an exposure index for each message type, for which the denominator will be the highest number of messages received by any one individual participant.Experience of intervention: Qualitative analysis will be carried out to assess participant experience of the study. A subset of participants and a support person (mother, mother-in-law, sibling, friend, or partner as determined by the woman) will be invited to participate in an interview upon completion of the 12-month postpartum follow-up visit. Approximately twenty participants per country are estimated to be required to achieve thematic congruence. This short interview (15–30 min) will explore their study experience, which will include their perception of the study, their experience of the impact, perceptions of core elements of the programme that were central to their experience, and any recommendations for further development of the intervention.

The RCT sits within the larger implementation project, and as such, much greater detail has been collected on the implementation aspects prior to the RCT commencing and the broader setting. Briefly, the project used the EPIS framework to scaffold the work [58]. The framework consists of 4 main components: exploration, preparation, implementation, and sustainment. The exploration phase involved evaluation of current needs to ensure the intervention fit across system levels, organisation levels, and staff and recipient levels. The preparation phase involved planning for the intervention through training, service mapping, and awareness. The implementation will be assessed using the RE-AIM framework [59], which measures results along the dimensions of Reach (to specified patient groups), Effectiveness (of the Bump2Baby and Me RCT), Adoption (by practice settings and clinicians), Implementation fidelity (consistency of delivery by various staff), and Maintenance (i.e. practices and results over the long term). Longitudinal interviews of key stakeholders at each clinical site will be carried out at quarterly intervals during the project. These semi-structured interviews will assess the local context and environment to measure what is happening within the hospital clinics and services that might impact the intervention and how well it fits with the current routine care. Qualitative thematic analysis of these interviews will enable the exploration of the Implementation and Sustainment components of the EPIS framework. This will be reported in an additional more detailed implementation protocol for the overall study.

### Statistical analyses

The intervention arm will be tested against usual care. Intention-to-treat (ITT) and a per-protocol set (PPS) analysis will be planned for both primary and secondary outcomes. Full analysis set is defined according to the ITT principle and will consist of all randomised subjects analysed according to the study arm to which they were assigned at randomisation, except for subjects who were randomised to the study in error and were subsequently excluded, e.g. twin pregnancies. The per-protocol set (PPS) will consist of all patients in the full analysis set without a major protocol deviation. Major protocol deviations include, but are not limited to, the following:
The subject was assigned to the intervention arm but did not reach minimum exposure. The minimal exposure requirement is that participants received the first onboarding session with the health coach.The subject did not have a post-baseline assessment.An eligibility criterion that was deemed to have been met at the time of randomisation was later found not to have been met.

Baseline characteristics will be compared between the intervention and control groups using the *χ*^2^ tests, the independent *t*-tests, and/or the Wilcoxon rank-sum test, as appropriate. Primary and secondary outcomes will be evaluated using repeated-measures analysis of variance (ANOVA) or mixed model analyses. Two-sided tests will be used, with a level of *P* < 0.05 determining statistical significance. Comparisons of the assessment times (the baseline and 12 months postpartum differences) within each treatment group (control or intervention) will be based on *t*-tests that utilise the standard errors of the differences that are computed as part of the repeated-measures analysis. Covariates included in the model will be kept to a minimum—site is the only covariate expected. The impact of loss to follow-up will be minimised by using a marginal model, which is not subject to list-wise deletion: each participant will contribute all time-specific measurements made to the model. Missing data will be reported for each outcome and handled by applying multiple imputation methods [60]. Subgroup analyses will be carried out to investigate the site differences based on the substantial demographic and operative differences in the four clinical sites. There are no interim analyses planned. Analyses will be conducted using the IBM SPSS software (version 26.0 or later; IBM), STATA version 12 or later (Stata Corp., College Station, TX, USA), or SAS software (SAS Institute Inc., Cary, NC, USA), as appropriate for analysis type. Data analysts will be blinded to group assignments.

A statistical analysis plan and data management plan have been prepared for the project which outlines plans for data entry, coding, confidentiality, security, and analysis in line with best practice (Additional file 2). Each clinical site is incorporated in this data management plan and provided the details to their relevant ethics committee. The project has an independent data manager who oversees the data monitoring and analyses and reports back to the RCT Working Group. There is no formal data monitoring committee; however, the external advisory board receives reports from the data manager.

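### The per-protocol set drops unexposed women from the intervention arm only, so its comparison is not protected by randomisation and can be biased

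*Protocol article*

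**What the plan says.** The Statistical analyses section plans both an intention-to-treat and a per-protocol analysis, each for the primary and the secondary outcomes. The full analysis set is to contain "all randomised subjects analysed according to the study arm to which they were assigned at randomisation". One group is left out of it, under this wording: "except for subjects who were randomised to the study in error and were subsequently excluded, e.g. twin pregnancies". The per-protocol set sits inside it: "The per-protocol set (PPS) will consist of all patients in the full analysis set without a major protocol deviation".

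Three major deviations are named, in a list described as open-ended:

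- Exposure: "The subject was assigned to the intervention arm but did not reach minimum exposure". The threshold follows: "The minimal exposure requirement is that participants received the first onboarding session with the health coach".
- Follow-up: "The subject did not have a post-baseline assessment".
- Eligibility: "An eligibility criterion that was deemed to have been met at the time of randomisation was later found not to have been met".

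The second and third can apply to a woman in either arm. The first can apply only in the intervention arm. The Sample size section commits the trial to intention-to-treat analysis. The Statistical analyses section does not rank the per-protocol result below it and does not mention the selection that the exposure rule creates. Site is the only covariate the article expects in the models.

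**The concern.** Whether a woman attends her first coaching session is behaviour that follows randomisation. Women who do not attend may differ from attenders in motivation, circumstances, health or weight trajectory. Randomisation puts about the same share of such women in each arm. The exposure rule then removes them from one arm and leaves their counterparts in the other, where they cannot be identified because no session was offered. The per-protocol difference therefore mixes any effect of coaching with the difference between attenders and the whole population.

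With site as the only expected covariate, the model has little to offset that difference. At stake is how a per-protocol result would be read. If it is larger than the intention-to-treat result, it will look like evidence that coaching works for those who take it up, when part or all of the excess could be selection.

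**Working it through.** The plan gives no figure for the effect of the exposure rule, so there is none to reproduce. The check asks what the rule does when the programme has no effect at all.

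**Inputs from the article (Sample size section).** Target difference 0.8 kg/m², SD 2 kg/m², 400 women per arm, 70% retention. Women with 12-month data per arm: 0.70 × 400 = 280.

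**Inputs assumed, because the article does not give them.**

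- p, the share of intervention women with 12-month data who missed the first coach session: 10% to 20%.
- D, the 12-month BMI of non-attenders minus that of attenders, as it would be without any programme effect: 1 to 2 kg/m² (0.5 to 1 SD).

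**Step 1, the shift.** Let A be the attenders' mean. The whole intervention arm has mean (1 − p)A + p(A + D) = A + pD. With no effect, the control arm has the same mean, A + pD. The per-protocol set keeps only attenders in the intervention arm, so the difference is A − (A + pD) = −pD.

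**Step 2, chance of a false positive.** With 280 controls and 280(1 − p) intervention women, SE = 2 × √(1/280 + 1/[280(1 − p)]). This is 0.174 for p = 10% (252 women) and 0.179 for p = 20% (224 women). The two-sided 5% error rate becomes Φ(−1.96 + pD/SE) + Φ(−1.96 − pD/SE).

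| p | D (kg/m²) | Spurious difference (kg/m²) | Share of 0.8 | Actual error rate (nominal 5%) |
|---|---|---|---|---|
| 10% | 1 | −0.10 | 12.5% | 8.9% |
| 10% | 2 | −0.20 | 25% | 21% |
| 20% | 1 | −0.20 | 25% | 20% |
| 20% | 2 | −0.40 | 50% | 61% |

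**Step 3, the same case under a complier estimate.** The complier average causal effect is the difference by allocation divided by the difference in the share who had the session, (1 − p) − 0. With no effect the numerator is expected to be zero, so the estimate is centred on zero for any p and D. Its standard error is about 1/(1 − p) times that of the intention-to-treat difference: 1.11 times at p = 10% and 1.25 times at p = 20%.

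**Step 4, the full analysis set.** If shares q₁ (intervention) and q₀ (control) are removed as randomised in error, and the removed women differ from those kept by d, the shift is −(q₁ − q₀)d. Equal removal, say 2% in each arm, gives zero. An assumed 5% against 2% with d = 2 gives −0.03 × 2 = −0.06 kg/m².

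**The case against.** The strongest reply is that the per-protocol set is not the lead analysis. The Sample size section commits the trial to intention-to-treat, and nothing says the per-protocol result decides the conclusion. Controls have no session to miss, so any exposure-based set is asymmetric, and this is a familiar limitation. That stands, and it limits the consequence. It does not remove the fault: the rule is stated, it is applied to the primary outcome, and no caution is attached. The open-ended list does not help, because no added control-arm criterion could identify the women who would have missed a session they were never offered.

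The size and direction are also assumed. Non-attenders could be lighter, and the sign would then reverse. The plan uses repeated-measures or mixed models that include baseline, so to the extent the effect is judged on change, a BMI gap already present at baseline would not carry through in full. D should be read as the part of the gap that the model does not absorb. Both points stand.

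Three stronger readings are tempting, and the article does not support them.

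- *An eligibility error that removes a woman from both sets is a fault.* It is not. The per-protocol set is nested in the full set, so whoever leaves the full set leaves both.
- *The two eligibility sentences contradict each other and bias the intention-to-treat comparison.* The wording overlaps, and a missed twin pregnancy fits both. But the full-set exception also requires that the woman was subsequently excluded. A woman withdrawn as wrongly randomised would leave the full set, while one found ineligible but kept would leave only the per-protocol set. The exception covers both arms, and a twin pregnancy is a fact that allocation cannot change. Bias would need discovery or exclusion to depend on arm, which is possible but not shown.
- *The exposure threshold is ambiguous because the Baseline assessments section says* "A researcher will facilitate participants in the intervention group with onboarding". The threshold is tied expressly to the health coach, and that section lists booking the initial coaching session as a separate step in the researcher's set-up.

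**Conclusion.** The point holds for the per-protocol set. Its exposure rule removes women from one arm on post-randomisation behaviour, so the planned per-protocol comparisons of primary and secondary outcomes are not protected by randomisation. With no true effect, and with 10–20% missing the session and non-attenders 1–2 kg/m² heavier than attenders, the spurious difference is 0.10–0.40 kg/m², or 13–50% of the 0.8 kg/m² target. The share, the gap and its direction are assumptions; the article gives none of them.

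The rule leaves the intention-to-treat analysis unaffected, and no bias in the full analysis set is shown. This is a correction worth making to a secondary analysis and does not threaten the trial's main result.

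**What to change.** 1. State that intention-to-treat is the lead analysis for all outcomes. Label the per-protocol analysis as supportive and not protected by randomisation.
2. Estimate the effect of receiving coaching by a complier average causal effect: two-stage regression with allocation as instrument, receipt of the first coach session as exposure, and adjustment for site and baseline BMI.
3. Report that estimate with its main weakness. It assumes that allocation acts only through the first session. This is imperfect, because women who miss the session may still receive app content and notifications.
4. As a tidy-up only, limit full-set exclusions to ineligibility shown by pre-randomisation facts and judged blind to arm. Treat other eligibility errors as per-protocol deviations only.

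The cost is a few lines of protocol or SAP wording and one standard extra analysis, with no effect on recruitment or participants. The complier interval is wider than the intention-to-treat interval, by about 11–25% under the assumed attendance. Baseline BMI is an addition to the single covariate the article now expects.
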